|                                                                                                   | Reduction in wound area and granulation area measurements                             | SAD+ MAD | Independent evaluators (photography)                                               | Wound area measurements (Section 11.8.4)                     |
| To assess the occurrence of wound rupture                                                         | Frequency of wound ruptures                                                           | SAD+ MAD | Investigator (direct observation)

Independent evaluators (photography)      | Wound rupture assessment (Section 11.8.3)                    |
| To assess scar tissue formation                                                                   | Overall scar tissue formation (normal/abnormal)                                       | SAD+ MAD | Investigator (direct observation)

Independent evaluators (photography)      | Overall assessment of scar tissue formation (Section 11.8.5) |
|                                                                                                   | Vancouver Scar Scale total score on Day 21 and onwards                                | SAD+ MAD | Investigator (direct observation)

Independent evaluators (photography)      | Vancouver scar scale (Section 11.8.5.1)                      |

| Objective                                                                                                                                      | Endpoint                                                                                             | Part        | Evaluator | Assessment(s)                                                                                                                                                                                                                      |
|------------------------------------------------------------------------------------------------------------------------------------------------|------------------------------------------------------------------------------------------------------|-------------|-----------|------------------------------------------------------------------------------------------------------------------------------------------------------------------------------------------------------------------------------------|

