### 8.1.1 *Single Ascending Dose (SAD)*

In Part I of the study, single topical doses of the IMP will be administered in 3 sequential cohorts of 4 subjects. For each subject, activated ILP100-DP and placebo will be randomized to experimentally induced wounds on the left and right arm in a 1:1 ratio (i.e. 2 wounds on one arm will be treated with activated ILP100-DP and 2 wounds on the other arm will be treated with placebo as randomized).

The proposed dose levels are:  $5 \times 10^4$ ,  $5 \times 10^7$  and  $1 \times 10^9$  CFU/cm^2 wound area. The rationale for the starting dose and the planned dose escalation is detailed in Section 8.3.

Subjects will come for 6 visits to the research clinic for screening, treatment and initial follow-up (Visit 1 to Visit 6), see Table 8.1-1 for details. After Visit 6, a 5-year long-term follow-up period (Visit 7 to 14) will be initiated as detailed below.

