The wounds will be photographed in a standardized setting according to instructions specified in a separate manual, and briefly summarized in Section 11.5, before treatment on Day 1 and at all subsequent visits to the research clinic. Selected members of the clinical staff will receive photography training prior to handling of the camera equipment. In addition, wounds will be analyzed using a 3D camera as outlined in Section 11.9.1.

Subjects will come back to the research clinic on Day 2, Day 3 and Day 7 (Visits 3 to 5) for safety assessments (vital signs, blood sampling for safety laboratory parameters [Day 2], local tolerability, AEs and use of concomitant medications), wound photography and blood

sampling for analysis of CXCL12 and *L. reuteri* exposure as detailed in Table 8.1-1. In addition, on Day 3, approximately 48 hours after IMP administration, the wound healing status will be assessed, a skin swab will be performed and one wound per arm will be removed by an 8 mm biopsy punch (the same wounds from all subjects) for histology analysis (see Section 11.8.2). Prior to biopsy punching, the subjects will be treated with local anesthesia. The residual 2 biopsy wounds will be closed using 1-2 surgical sutures and dressed as appropriate. The other 2 wounds (one per arm) will be left untouched for continued evaluation.

The wounds must not at any visit be cleaned (unless necessary for safety reasons, e.g. due to an infection). The area surrounding the wounds should then be carefully cleaned with water if necessary. At visits when swabbing is performed, the area around the wound should be cleaned after swabbing if necessary. Before the subject leaves the research clinic, the wound should be dressed until healed.

An end-of-treatment phase visit (Visit 6) will take place on Day 14 ( $\pm 1$  day) or after early withdrawal. For details on assessments, see Table 8.1-1 and Section 11.

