15. CXCL12 blood sampling at 9:00±2 hours. On Day 2: 24h±2 hours post dose but no later than 11:00. On Day 3 and 14, also plating of blood samples prior to centrifugation for blood culturing, see Section 11.8.1 and Section 11.8.1.2.
16. 48 hours after IMP administration (one biopsy from a CXCL12 treated wound and one from a placebo treated wound)
17. Wound healing assessed by the Investigator (direct observation) and by 3 to 5 independent evaluators using photographs.
18. Wound area assessed by 3 to 5 independent evaluators using photographs and the Image J software (National Institutes of health [NIH]) or equivalent.
19. Baseline wound area measurements based on photos taken after wound punching prior to IMP application.
20. Scar tissue formation assessed by the Investigator (direct observation) and by 3 to 5 independent experts using photographs at Visit 6. Scar tissue formation during the long-term follow-up assessed by the Investigator only. Normal/abnormal and Vancouver scar scale. One assessment per wound.
21. Dressing if indicated.
22. From administration of IMP.
23. Collection of AEs including, but not limited to, mortality, development of any new/recurrent cancer, development of infection, immunogenicity related reactions.
24. For definitions of prior and concomitant medications, see Section 11.3.6.

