14. CXCL12 blood sampling prior to wound punching at 9:00±2 hours, 1 hour post the last wound punch (within 5 minutes of start of IMP application, which should start 1 hour (+/-10% post the last wound punch) and 1 hour (±10%) after the last IMP application.
15. Pre-treatment. The pre-treatment sample should be taken at 9:00±2 hours.
16. Pre-treatment on Day 5, 8, 15 and 19. The pre-treatment samples should be taken at 9:00±2 hours.
17. On Day 3, 5, 8, 15 and 21, also plating of blood samples prior to centrifugation for culturing, see Section 11.8.1 and Section 11.8.1.2.
18. The CXCL12 blood sample should be taken at 9:00±2 hours.
19. Pre-dose Day 1 and pre-dose on Day 19, see Section 11.8.1.
20. Wound healing assessed by the Investigator (direct observation) and by 3 to 5 independent experts using photographs. No assessment by independent experts on Day 17.
21. Wound area assessed by 3 to 5 independent experts using photographs and the Image J software (NIH) or equivalent.
22. Baseline wound area measurements based on photos taken after wound punching prior to IMP application.
23. Scar tissue formation assessed by the Investigator (direct observation) and by 3 to 5 independent experts using photographs Visit 9 to Visit 12. Scar tissue formation during the long-term follow-up assessed by the Investigator only. Normal/abnormal and Vancouver scar scale. One assessment per wound.
24. Day 5, Visit 5.
25. Day 15, Visit 9.
26. At any time between Day 15 and Day 21.
27. Just prior to treatment on Day 2, Day 8 and Day 15.
28. Dressing if indicated.
29. Dressing collection on Day 2 (applied Day 1), Day 3 (applied Day 2).
30. From administration of IMP.
31. Collection of AEs including, but not limited to, mortality, development of any new/recurrent cancer, development of infection, immunogenicity related reaction.
32. For definitions of prior and concomitant medications, see Section 11.3.6.

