#### **11.4 Wound punching/biopsy**

At Visit 2 (Day 1) of each part, standardized full-thickness punch biopsy wounds (6 mm in diameter) will be produced under local anesthesia on the right and left inner arm (2 wounds per arm in the SAD part and 4 wounds per arm in the MAD part).

In the SAD part, one wound punch biopsy per subject will be saved for baseline histology analysis using the procedure described in Section 11.8.2. In addition, on Day 3 of the SAD part, approximately 48 hours after dose, punch biopsies (8 mm) from one wound per arm will be sampled under local anesthesia (injected and/or topical) and saved for histological analysis as described in Section 11.8.2.

Subjects will be treated with local anesthetics (injected and/or topical) in accordance with the manufacturer's instructions and each upper inner arm will be cleaned with 70% ethanol prior to wound incision. The wounds should be placed at least 4 cm apart. Each wound will be labelled with a permanent marker (SAD: L1 to L2 on the left arm, R1 to R2 on the right arm, MAD: L1 to L4 on the left arm and R1 to R4 on the right arm). The position of each number will be the same in all subjects). Subjects will be instructed to fill in the numbering as necessary (at least once weekly up until and including Visit 6 in the SAD part and Visit 13 in the MAD part).

Following wound incision, compression for hemostasis will be applied if necessary. In case of excessive bleeding (which is rare but may occur), where hemostasis is not achieved by compression, diathermy may be used to stop the bleeding. If diathermy is used, this should be noted in the eCRF. The subject may be treated with IMP as planned once hemostasis is achieved. There should be 1 hour ( $\pm 10\%$ ) between the last wound punch and the start of IMP application to allow for pre-dose study assessments and hemostasis. For details on IMP application, refer to Section 10.6. The wound punching procedure will be detailed in a separate manual.

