#### **17.6.4 *Wound area***

The reduction in wound area will be presented using summary statistics by treatment, visit and cohort. Dose response relationship will be presented by correlation analysis. Comparison between active and placebo treatment will be performed by ANOVA.

All data will be listed by cohort, treatment and subject.

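### Wound area is compared by ANOVA with the endpoint expressed as a reduction and no Day 1 area term named; this can cost precision, though it causes no bias

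*Protocol*

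**What the plan says.** The secondary endpoint in section 7.2.1 is "Reduction in wound area and granulation area measurements". Section 17.6.4 then gives the analysis in two steps: "The reduction in wound area will be presented using summary statistics by treatment, visit and cohort", followed by "Comparison between active and placebo treatment will be performed by ANOVA". It names no covariate, does not list the factors in the ANOVA, and does not say whether the reduction is absolute or a percentage.

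A baseline value exists for every wound. The footnotes to both schedules of events say: "Baseline wound area measurements based on photos taken after wound punching prior to IMP application". The same evaluators who trace the later photographs supply it: "Wound area assessed by 3 to 5 independent evaluators using photographs". Area is then measured up to Day 14 in the SAD part and Day 21 in the MAD part.

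Section 11.4 makes every wound with a standardized 6 mm punch. The SAD part has "3 sequential cohorts of 4 subjects", and after the Day 3 biopsies one active and one placebo wound per subject remain (section 8.1.1: "The other 2 wounds (one per arm) will be left untouched for continued evaluation"). The MAD part has three cohorts of 8. Section 9.9 randomizes treatment by arm, so each subject carries both treatments. Section 17.2 reports no sample size calculation.

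**The concern.** A change score subtracts the whole of the measured baseline. That is efficient only when follow-up area rises one for one with baseline area. Two features of this trial make that unlikely.

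First, true wound size is fixed by the punch, so differences between wounds in traced Day 1 area should come largely from tracing, bleeding and skin retraction. Subtracting them adds noise.

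Second, area is measured over a period in which wounds may close, and in the MAD part section 8.2 continues dosing whatever the healing status. For a closed wound the absolute reduction is simply its own Day 1 area. Once most wounds have closed, the ANOVA mainly compares Day 1 tracings between arms.

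At stake is the width of the interval around an active-placebo contrast that rests on 4 (SAD) or 8 (MAD) subjects per dose. The information needed to narrow it is already collected.

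**Working it through.** The protocol states no SD, correlation or power for wound area, so there is no figure to reproduce. What follows rests on assumed values.

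**Inputs from the protocol.** Nominal area is π × 0.3² = 0.283 cm² for every wound (Table 8.3-1 gives 0.28). There are 4 subjects per SAD cohort and 8 per MAD cohort, with three cohorts in each part.

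**Assumed inputs.** k = SD(baseline) / SD(follow-up), and ρ = the correlation between them.

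**Large-sample variance.**
- Change score: σ₀² + σₜ² − 2ρσ₀σₜ
- Baseline-adjusted: σₜ²(1 − ρ²)
- Ratio: (1 + k² − 2ρk) / (1 − ρ²) = 1 + (k − ρ)² / (1 − ρ²)

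The second form shows that the ratio is never below 1 and equals 1 exactly when ρ = k.

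| k | ρ | Variance ratio, change / adjusted |
|---|---|---|
| 0.5 (follow-up more variable) | 0.1 to 0.5 | 1.16 down to 1.00 |
| 1 | 0.1 to 0.7 | 1.82 down to 1.18 |
| 2 (late healing) | 0.1 to 0.5 | 4.65 down to 4.00 |

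Worked example, k = 1 and ρ = 0.3: (1 + 1 − 0.6) / (1 − 0.09) = 1.40 / 0.91 = 1.54.

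**Limiting case.** If follow-up area is 0, absolute reduction = Day 1 area − 0 = Day 1 area. Its spread is then entirely baseline spread. Percent reduction is 100% for any closed wound, so this limiting case applies to absolute reduction only. For open wounds a percentage still divides by the noisy baseline.

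**Small samples.** The formula ignores the degree of freedom spent on the slope, so interval widths were simulated. Each subject contributes one active-minus-placebo difference at baseline and one at follow-up, and k and ρ here refer to those differences. The entries are the median 95% half-width with adjustment divided by that without, over ρ = 0 to 0.75.

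| Fit | k = 0.25 to 1 | k = 2 |
|---|---|---|
| One SAD cohort alone, 4 pairs | 1.06 to 1.51 | 0.67 to 0.75 |
| One MAD cohort alone, 8 pairs | 0.78 to 1.10 | 0.49 to 0.55 |
| SAD, common slope and pooled error, 3 × 4 | 0.75 to 1.07 | 0.48 to 0.54 |
| MAD, common slope and pooled error, 3 × 8 | 0.73 to 1.03 | 0.46 to 0.51 |

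In the last two rows both analyses pool the error across cohorts, and the contrast is for one cohort. The reason for the difference is the t quantile. In a single 4-subject cohort, going from 3 to 2 degrees of freedom raises it from 3.18 to 4.30. With the three SAD cohorts fitted together, going from 3 × 3 = 9 to 8 raises it only from 2.26 to 2.31.

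**The case against.** The strongest reply is that section 17.6.4 says only ANOVA. Section 17 confines itself to principal features and leaves the detail to an SAP, where covariates are normally set. A reader might infer that the plan rules out baseline adjustment. It does not, and a sound SAP could add the term. What stands is narrower: the protocol names both the form of the outcome and the test, and an SAP that follows those words literally would use the less efficient analysis.

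A reader might also infer that the comparison is biased, or that chance differences in punch size distort it. The documents do not support that. Treatment is randomized by arm, the punch is standardized, and ANOVA on the reduction is a valid comparison.

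The small-sample objection is correct as far as it goes. Adjusting within a single 4-subject cohort widens the interval by 6% to 51% for k up to 1, so an unrestricted recommendation to add the covariate would do harm there. This governs how the covariate is fitted; it is not a reason to leave it out.

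Two further limits stand. At late visits many areas sit at zero, where a linear model for area has floor effects of its own, so the largest ratios should be read with caution. And wound area is not the only continuous efficacy measure: granulation area, the Vancouver total score and the exploratory 3D measures are also continuous.

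**Conclusion.** The point holds as one about efficiency on a secondary endpoint. The protocol pairs a reduction endpoint with ANOVA and names no baseline term, although a pre-dose area exists for every wound. In large samples the absolute change score is never more precise than the baseline-adjusted contrast, and with a fixed punch size it may be less precise, most of all at late visits.

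The size cannot be determined from the protocol. Across the assumed SD ratios and correlations tabulated, the variance ratio runs from 1.0 to about 4.7. It is tempting to say that precision is certainly lost, or from the ratio of 1.54 that 8 subjects carry the information of about 5 (8 / 1.54 = 5.2). Neither follows. The loss is zero when ρ = k, and 1.54 is one assumed setting that ignores the degree of freedom. In a single 8-subject cohort with k up to 1, the adjusted interval ranges from 22% narrower to 10% wider.

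**What to change.** In section 17.6.4, or in the SAP before the interim report it supports, specify the following:

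- Compare wound area at each visit between active and placebo in a subject-level (within-subject) model, with the Day 1 area measured after punching and before dosing as covariate.
- Within each part, use one baseline slope and pooled error across the three cohorts. Do not fit the covariate separately in each 4-subject SAD cohort.
- Keep absolute and percent reduction as descriptive summaries by treatment, visit and cohort.

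No new data are needed. The cost is one degree of freedom per part. In the settings simulated, the interval is at worst about 7% wider in the SAD part and 3% wider in the MAD part. At k = 2 it is roughly halved.

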#### **17.6.5 *Scar formation***

Overall scar tissue formation (normal/abnormal) will be presented using summary statistics by treatment, visit and cohort.

Each individual item will be presented using frequency tables by cohort, treatment and visit. The total score will be presented using summary statistics by cohort, treatment and visit.

All data will be listed by cohort, treatment and subject.

#### **17.6.6 *Detection of *L. reuteri* colonies on skin***

*L. reuteri* R2LC colonies on skin will be presented using summary statistics by treatment, visit and cohort.

The colonies will be presented both as actual values and by logarithm scale (10 log).

All data will be listed by cohort, treatment and subject.

#### **17.6.7 *Detection of *L. reuteri* colonies in feces***

*L. reuteri* R2LC colonies in feces be presented using summary statistics by treatment, visit and cohort.

The colonies will be presented both as actual values and by logarithm scale (10 log).

All data will be listed by cohort and subject.

## **17.7 Analysis of exploratory endpoints**

The exploratory endpoints may not be reported in the CSR.

### **17.7.1 *Changes in wound and scar appearance by 3D imaging***

3D imaging data will be presented using summary statistics by treatment, visit and cohort.

All data will be listed by cohort, treatment and subject.

### **17.7.2 *Microcirculation analysis***

Data will be presented using summary statistics by treatment, visit and cohort.

All data will be listed by cohort, treatment and subject.

### **17.7.3 *Wound microbiome alterations***

Data will be presented using summary statistics by treatment, visit and cohort.

All data will be listed by cohort, treatment and subject.

## **19.2 Declaration of Helsinki**

[http://www.up.ac.za/media/shared/Legacy/sitefiles/file/45/2875/declarationofhelsinki\\_fortaleza\\_brazil2013.pdf](http://www.up.ac.za/media/shared/Legacy/sitefiles/file/45/2875/declarationofhelsinki_fortaleza_brazil2013.pdf)
